#### 10.1.2 CONFIDENTIALITY AND PRIVACY

Participant confidentiality and privacy is strictly held in trust by the DRES-POCAI study investigators, staff, and the sponsor(s). This confidentiality is extended to cover the clinical information relating to participants. Therefore, the study protocol, documentation, data, and all other information generated will be held in strict confidence. No information concerning the study, or the data will be released to any unauthorized third party without prior written approval of the sponsor.

All research activities will be conducted in a private office.

The study monitor (e.g., Multi-Specialty Quality Review Committee - *MSQRC*), other authorized representatives of the sponsor, representatives of the IRB, regulatory agencies may inspect all documents and records required to be maintained by the investigator, including but not limited to, medical records

(office or clinic) and DR screening records for the participants in this study. The clinical study site will permit access to such records.

The study participant's contact information will be securely stored at each clinical site for internal use during the study. At the end of the study, all records will continue to be kept in a secure location for as long a period as dictated by the reviewing IRB, organization's policies, or sponsor requirements.

Research data collected will be coded with a participant's unique identifier, or number. Personal identifying data will not appear on any research data. As is true for all SYHealth, UC San Diego personnel, and any person(s) working on this research project will have undergone extensive orientation and training on issues regarding the maintenance and protection of confidentiality (e.g., sending confidential material to a community printer, using names while conducting phone interviews, etc.)

Protecting participant confidentiality is a fundamental principle of SYHealth and this study. The study will employ strict measures to safeguard sensitive health information. These include secure storage of all study records with access limited to authorized research personnel. For analysis and reporting, participant data will be de-identified, and unique study codes will be assigned. The link between codes and participant names will be kept in a separate, secure location and will be accessible only to selected SYHealth personnel (PIs, Co-I, and Program Manager). Data transmission to research partners will utilize secure protocols, and data will be de-identified prior to sharing. Any relevant details about study participation (e.g., screening results) will be added to the participant's SYHealth medical records to ensure continuity of care. In accordance with SYHealth policies and standard privacy laws, participants retain the right to access their medical records, but some research-specific information may be inaccessible to them (e.g., survey responses).

Study findings may be published or shared at conferences, but individual participant information will always remain confidential. De-identified data collected during the study might be used for future research or shared with other scientists, but no personal identifiers will be included. Participants will sign a HIPAA Research Authorization form to permit the use of their protected health information in this study. This also facilitates continuity of care related to any study outcomes.

---

### 10.1.3 FUTURE USE OF STORED SPECIMENS AND DATA

De-identified data collected during the study might be used for future research or shared with other scientists, but no personal identifiers will be included.

#### 10.1.5 SAFETY OVERSIGHT

Safety oversight will be under the direction of a Data and Safety Monitoring Committee (DSMC) composed of individuals with the appropriate expertise, including faculty from academic institution (i.e., San Diego State University) that are leaders of federally funded research projects, SYHealth medical expert with experience clinical research, member of the quality department with expertise in risk management, member of the quality analytics team, and the coordinator of the SYHealth Research Review Committee with extensive experience in Ethical and Responsible Conduct of Research and Human Subjects Protection program at SYHealth. Members of the DSMC are independent from the study conduct and free of conflict of interest, in addition, measures will be in place to minimize perceived conflict of interest. The DSMC will meet at least semiannually to assess safety and efficacy data on each arm of the study. The DSMC will operate under the rules of an approved protocol that will be written and reviewed at the organizational meeting of the DSMC. At this time, each data element that the DSMC needs to assess will be clearly defined. The purpose of the DSMC of the DRES-POCAI study will be to 1) periodically review and evaluate the accumulated study data for participant safety, study conduct and progress and efficacy, 2) assess all adverse events reported during the course of the study and 3) make recommendations concerning the continuation, modification, or termination of the study. The DSMC will consider study-specific data as well as relevant background knowledge about the disease, intervention, or target population under study.

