## STATISTICAL METHODS

**Sample Size and Power Calculations:** Based on historical data from participating SYH clinics, we determined that approximately 59% of patients completed diabetic retinopathy screening, we powered our study to detect an increase of at least 10% in retinopathy screening completion (59% in the standard of care group to 69% in the intervention group), and assuming an  $\alpha$  of 0.05 (significance) and a  $\beta$  of 0.8 (power), we estimated that the target enrollment to detect this difference is 722 participants (361 per arm) using a two independent sample Pearson  $\chi^2$  test. Accounting for up to 15% attrition from consent to study intervention (participants who agree to participate and consent via phone, and either do not keep their appointment or who at the clinic appointment decide to withdraw from the study), we estimated as many as 848 patients (424 per arm) would need to be enrolled to ensure adequate sample size. To assess secondary outcomes, we determined that among the patients who underwent retinal screening within the previous 12 months at the participating SYH clinics, 11% were diagnosed with diabetic retinopathy; therefore, based on a screening uptake increase of 10%, a corresponding 16% increase in diabetic retinopathy diagnosis is anticipated in the intervention arm. However, if after the initial refinement

phase of the project, it is determined that either a smaller or larger percent of the target population is currently completing DR screening, we will adjust the study enrollment accordingly, to ensure we will have sufficient statistical power to evaluate the anticipated 10% increase in screening uptake.

**Statistical significance and transformation of variables:** All statistical tests will be two-sided unless defined otherwise. Statistical significance will be set at  $p$ -value  $<0.05$ . Where distributional assumptions are necessary for the correct evaluation of statistical results, appropriate description, diagnostic evaluation, and (if required) transformation of variables will be carried out. In the event the parametric tests indicated are unable to be used, non-parametric versions will be used.

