## DATA MANAGEMENT

**Methods for data collection:** Data will be captured using electronic record forms in REDCap. EMR data will be extracted and entered into REDCap forms by study personnel and participants will complete survey questionnaires using study provided electronic tablets.

**Data quality and standards:** The quality of data collection and data entry will be maximized through training of staff in both administration of the intervention and the standardized questionnaire administration. Study staff will be trained in the data collection and will be expected to demonstrate competence before extracting data from the EHR.

Verified and validated data will be stored on secure, fault-tolerant network servers at San Ysidro Health. Data will be backed-up on a continuous basis on a secure off-site server and on encrypted standalone hard drives. Once the data validation phase has been completed, the database will be locked and transferred to a statistical programmer who will do further syntax-driven consistency checks and syntax-driven data cleaning.

The study programmer will have access to the original copies of the source data. He/she will then prepare the database for data analysis by the statistician by generating the final variables for data analysis, such as the construction of the composite endpoints. The final cleaned database will be available with a corresponding data dictionary.

**Safety analysis and data monitoring:** No formal safety endpoints will be analyzed. However, all documented adverse events will be recorded and presented to the Data Safety Monitoring Committee (DSMC) and in the final report detailing the date, description, resolution, follow-up, and outcome.

To ensure participant safety and study integrity, the DSMC will meet quarterly to review recruitment progress, data quality, and protocol adherence, and to advise on managing any special circumstances.

**Interim Analyses:** No formal interim analysis for efficacy is planned.

**Statistical analysis software:** Data will be cleaned using MS Excel and analyzed using STATA.

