**Intervention Data Collection and Monitoring, and Quality Assurance.** This is part of the Quality Control and Quality Assurance (QC/QA) protocols of the study. It includes the collection of study data related to safety outcomes, intervention efficacy, and participant characteristics. The study DA and leadership will also conduct regular monitoring of study data to ensure accuracy, completeness, and integrity. They will meet every week to review the weekly reports and discuss the progress of the intervention. In addition, the study coordinator will conduct observations and QC/QA audits to monitor study staff adherence to the study protocol and SOPs. The implementation of the study's QC/QA measures will ensure the overall integrity and reliability of study data and procedures. The study team will conduct regular audits and reviews to identify and address any potential issues implementing the corrective actions and training needed (**SOP Quality Control and Quality Assurance**).

**Data Safety and Monitoring Committee (DSMC).** The study will also have an internal Data Safety and Monitoring Committee. The committee's members will include faculty from academic institutions (i.e., San Diego State University and UC San Diego) that are principal investigators or co-investigators of federally funded research projects, SYHealth medical experts with experience in clinical research, SYHealth quality department members with expertise in risk management, SYHealth quality analytics staff, and the coordinator of the SYHealth's Research Review Committee with extensive experience in Ethical and Responsible Conduct of Research and Human Subjects Protection programs. The purpose of the DSMC is to 1) periodically review and evaluate the accumulated study data for participant safety, study conduct and progress and efficacy, 2) assess all adverse events reported during the course of the study and 3) make recommendations concerning the continuation, modification, or termination of the study. The DSMB will consider study-specific data as well as relevant background knowledge about the disease, intervention, or target population under study.

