#### 9.4.1 GENERAL APPROACH

**Descriptive Statistics:** Categorical data will be presented as frequencies and percentages. Based on normality assessments, continuous data will be presented as means (standard deviations) or medians (interquartile range). Patient characteristics will be presented using descriptive statistics and compared between intervention and standard of care groups using two-sample t tests for continuous (normally distributed) variables and Pearson's chi-squared test will be used for binary and categorical variables.

**Inferential Tests:** The impact of the intervention will be assessed by comparing the outcome of interest between intervention and usual care groups using logistic or poisson regression (depending on distribution of outcome) and adjusting for identified covariates and assessing study intervention arm as the primary independent variable. A significant level (p-value) of 0.05 will be used with 95% confidence intervals reported. Two-tailed tests will be conducted unless there is a strong a priori basis for a one-tailed test.

**Covariates:** Covariates will be assessed individually between intervention and usual care groups and by outcome of interest. We will use Hosmer and Lemeshow's covariate inclusion approach (purposeful selection at each modeling step) when developing models to ensure inclusion of biologically and statistically relevant variables.

**Assumptions:** Data will be checked for normality of distribution prior to analysis. If assumptions are violated, appropriate transformations will be applied, or non-parametric tests will be used.

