#### 10.1.1 STUDY DISCONTINUATION AND CLOSURE

The DRES-POCAI study may be temporarily suspended or prematurely terminated if there is sufficient reason to do so. Circumstances that could warrant suspension or termination include unexpected safety concerns for participants, demonstration of overwhelming efficacy that necessitates providing the superior intervention to all, evidence that the study intervention is unlikely to demonstrate the intended effect, insufficient compliance with study protocols, data quality issues, or decisions by the sponsor, funding agency, or regulatory bodies.

This study may be temporarily suspended or prematurely terminated if there is sufficient reasonable cause. If the study is prematurely terminated or suspended, the Principal Investigator (PI) will promptly inform study participants, the Institutional Review Board (IRB), and sponsor and will provide the reason(s) for the termination or suspension. Study participants will be contacted, as applicable, and be informed of changes to the study visit schedule.

A suspended study may resume once any concerns about safety, protocol compliance, and data quality are addressed to the satisfaction of the sponsor, IRB, and relevant regulatory agencies.

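### The protocol lets the monitoring committee see efficacy by arm and lists overwhelming efficacy as a reason to stop, yet no interim analysis or boundary is written, so no stated rule controls type I error

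*Combined protocol and SAP*

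**What the plan says.** **Text that opens a route to stopping on efficacy**
- Protocol 10.1.5: "The DSMC will meet at least semiannually to assess safety and efficacy data on each arm of the study". The committee may recommend that the trial continue, change or end.
- Protocol 8.2 gives it the same remit: to "periodically review and evaluate the accumulated study data for participant safety, study conduct and progress and efficacy".
- Protocol 10.1.1 names, among the reasons for ending the trial early, "demonstration of overwhelming efficacy that necessitates providing the superior intervention to all". It also names evidence that the intervention will probably fail to show its effect. Neither has a threshold.

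**Text that says there is no such route**
- SAP, Interim Analyses: "No formal interim analysis for efficacy is planned".
- Protocol 4.1 and 9.4.6 mark interim analysis as not applicable.
- SAP, Safety analysis and data monitoring: "the DSMC will meet quarterly to review recruitment progress, data quality, and protocol adherence". The same section also sends adverse events to the committee. Efficacy is the item missing from the SAP's remit.

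**The final test**
- Protocol 9.4.1: "A significant level (p-value) of 0.05 will be used with 95% confidence intervals reported". SAP: "All statistical tests will be two-sided unless defined otherwise". Neither adjusts for earlier looks.

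**Deferred rules**
- Protocol 10.1.5 says the committee will work under its own protocol, to be written at its organizational meeting, when the data elements it needs will be defined. A stopping boundary is not mentioned.

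**The concern.** A 5% error rate holds for one test at the end. If comparative efficacy data are seen during the trial and can lead to a stop and a claim of benefit, each such look is another chance of a false positive. Whether the look is called formal does not change this. What matters is whether the trial can stop because of it, and the protocol text allows that.

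The design adds a second problem. Under protocol 4.4 and 6.1.1, the intervention arm is screened with the AI system on the day of the study visit, while usual care is screened on another day at another place. The primary window is 3 months in the SAP and 60 days in protocol 9.4.2. During recruitment the intervention arm's outcome is known almost at once and the usual-care outcome is still accruing. A by-arm table of everyone enrolled so far would show a gap even if the final completion rates were equal.

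**Working it through.** **1. The plan's own figure.** Inputs from the SAP sample size section: 59% versus 69%, two-sided 0.05, 80% power, 1:1.

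n per arm = [1.960 × √(2 × 0.64 × 0.36) + 0.8416 × √(0.59 × 0.41 + 0.69 × 0.31)]² / 0.10²
= (1.3305 + 0.5682)² / 0.01 = 360.5, rounded up to 361.

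This reproduces 361 per arm and 722 in total. It is a fixed design with one test and no allowance for interim looks.

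**2. Overall two-sided error if efficacy looks can stop the trial.** The documents give neither the number of looks nor the threshold, so both are assumptions. The error is the probability that |Z| crosses its limit at any analysis when there is no true difference, found by numerical integration over the joint distribution of the successive Z statistics. The limit is 1.96 for nominal 0.05 and 3.29 for p<0.001.

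The rows for 12-month recruitment rest on the 1-year participant duration within a 2-year study. At months 6 and 12 the information fractions are (6−3)/12 = 0.25 and (12−3)/12 = 0.75 with a 3-month window, or (6−2)/12 = 0.33 and (12−2)/12 = 0.83 with 60 days.

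| Analyses, including the final one | 0.05 at every look | p<0.001 at interims, 0.05 at the end |
|---|---|---|
| 2, equally spaced | 8.3% | 5.0% |
| 3, at 0.33, 0.83 and 1 of the information | 10.3% | 5.1% |
| 3, at 0.25, 0.75 and 1 | 10.9% | 5.1% |
| 4, equally spaced (every 6 months for 2 years) | 12.6% | 5.1% |

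**3. The open-window effect.** Illustrative assumptions:
- True completion is 59% in both arms at 3 months.
- AI completions are immediate, and usual-care completions are spread evenly over 3 months.
- The 848 participants are enrolled evenly over 12 or 18 months.

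At month 6, participants enrolled in the first 3 months have a full window and the rest have on average half of one. Usual care therefore shows 59% × (3 + 1.5)/6 = 44%, against 59% in the intervention arm.
- 12-month recruitment: 848 × 6/12 = 424, or 212 per arm; Z = 3.04, p = 0.002.
- 18-month recruitment: 848 × 6/18 = 283, or about 141 per arm; Z = 2.48, p = 0.013.

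At month 3, which the words *at least* would permit, usual care shows 59% × 0.5 = 29.5% and p is below 0.001 in both cases. A strict p-value alone does not protect against this. The look must be limited to completed windows.

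**The case against.** The strongest reply is that nothing in the documents says the trial will stop at nominal p<0.05. The word *overwhelming* points to a strict bar, under which the error is about 5.1%. A plan with no formal interim analysis is also compatible with descriptive review, and the committee's own protocol could still set a boundary. All of this stands as far as size goes, and it is why no single inflation figure can be given. It does not remove the gap. The strict bar is not stated, 10.1.5 promises defined data elements but no boundary, and a boundary set there would still conflict with the SAP and 9.4.6.

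Some stronger readings are tempting but unsupported:
- **Efficacy is reviewed every quarter.** Eight analyses at nominal 0.05 would give 17.6%. Only the meeting held at least semiannually is tied to efficacy; the SAP's quarterly meeting is not.
- **The two meeting frequencies contradict each other.** Quarterly meetings satisfy a minimum of semiannual ones.
- **The futility ground inflates type I error.** It does not. Without a criterion it can cost power.
- **An early stop would end the diagnosis and 6-month outcomes.** The documents do not say so, and screening and diagnosis are extracted from the health record.

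The open-window effect is likewise conditional: no section says that participants with incomplete windows would be tabulated. Equally, no section excludes them.

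**Conclusion.** The conflict is real. The protocol combines by-arm efficacy review, a power to recommend termination and an efficacy ground for stopping, while the statistical sections of both documents assume a single unadjusted test. The 5% error rate is not controlled by any written rule.

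The size is unknown. On assumed semiannual looks it runs from about 5.1%, if interim stopping requires p<0.001, to about 8% to 13%, if 2 to 4 analyses are each tested at 0.05. The upper figures depend on a stopping rule that nobody has written, so they show what the text leaves open; they do not predict what will happen. The open-window bias is separate and is not part of these error rates. It follows from the different timing of screening in the two arms, and it arises only if a look includes participants whose window has not elapsed.

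This should be corrected. It does not by itself undermine the design.

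**What to change.** **Simplest: make the protocol match the SAP.** Remove comparative efficacy from the committee's remit in 8.2 and 10.1.5, and remove the efficacy and futility grounds from 10.1.1. Alpha stays at 5% and the analysis sample at 722. The price is that the trial cannot stop early for benefit, which is modest given that the protocol describes the screening as minimal risk.

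**If an efficacy stop is wanted**, state in the SAP and in protocol 9.4.6:
- a Haybittle-Peto threshold of p<0.001 on the primary outcome at any interim look, with 0.05 at the end (overall error about 5.1% for up to four analyses);
- that the look includes only participants whose full primary window has elapsed, in both arms, which requires first reconciling the SAP's 3 months with the protocol's 60 days;
- that futility advice is non-binding.

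Because the final test stays at 0.05, this boundary does not raise the sample size. The price is that only a very strong result could stop the trial.

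Stating one meeting frequency in both documents would be tidy, but it does not correct an error. All of these are wording changes.

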#### 10.1.6 CLINICAL MONITORING

The DRES-POCAI study clinic sites monitoring will be conducted to ensure that the rights and well-being of trial participants are protected, that the reported trial data are accurate, complete, and verifiable, and that the conduct of the trial is in compliance with the currently approved protocol/amendment(s), with International Conference on Harmonization Good Clinical Practice (ICH GCP), and with applicable regulatory requirement(s), e.g., SYHealth clinical guidelines.

The Clinical Monitoring Protocol (CMP) establishes the guidelines for conducting monitoring visits and related tasks for monitoring Diabetic Retinopathy Screening Point-of-Care Artificial Intelligence - DRES-POCAI Protocol number 810204. The CMP was developed by San Ysidro Health Quality and data analytics

team, in collaboration with the Multi-Specialty Quality Review Committee (MSQRC) and the Principal Investigator (PI). The MSQRC group is a multi-disciplinary team composed of clinical experts in primary care and behavioral health, risk management, quality, and operations. Moreover, two of the team members are the Director of behavioral health services and the director of the residency program with extensive experience in clinical research. The Monitoring Team (Quality Manager and Data Analytics Manager) is part of the MSQRC with the main purpose to ensure the study is conducting in compliance with the clinical guidelines and SYHealth's policies and procedures for clinic operations and patient care (as applicable). The Monitoring team will be responsible for performing the monitoring tasks in accordance with the protocol specific requirements.

